### Data analysis

#### Analysis of primary Endpoin

The primary endpoint is the incidence of acute grade ≥ 2 GU toxicity on the CTCAE v 4.03 scale. Acute toxicity rates will be reported descriptively. Point estimates as well as the associated 95% confidence intervals (CIs) will be reported. Comparison between study arms will be performed via Chi-square test or fisher’s exact test.

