### Selection, study enrolment and randomization procedures

Patients seen as new patients in consultation in the UCLA Radiation Oncology clinic who are being evaluated for potential definitive radiotherapy for prostate cancer options will be informed of this clinical study if eligible. An informed consent form will be given to the patient for review. Upon confirmation of eligibility and enrollment in the study, the following will be obtained: (1) Medical history, clinical examination and consultation with Radiation Oncology; (2) Signed informed consent. Whenever feasible and in the best interest of the subject, the clinical examination, consultation and informed consent discussion and consent form signing may occur via telemedicine.

After the patient eligibility form is filled out in the Research Electronic Data Capture (REDCap) system, patients were randomly assigned to the two arms by a reproducible computer code developed by the UCLA Department of Medicine Statistics Core (DOMStat). To ensure balance between treatment allocation, stratified permuted blocked randomization will be used. The block sizes used will be blinded to the radiation oncology research team when enrolling a patient. The allocation result will not be released until after the screening/baseline data are filled out in REDCap (no anticipation of the group assignment will be possible). To obtain adequate “allocation concealment”, a list of random allocations has been created for patients 1 through 300. This list will be stored in REDCap and will not be modified.

Randomization will be stratified by the baseline IPSS (≤15 or > 15) and prostate gland volume (≤50 cc or > 50 cc). Prostate gland volume will be determined with MRI, which is mandatory. For analysis of the secondary endpoints of acute and late physician-scored toxicity, as well as bowel-related patient-reported outcomes, the analysis will be further stratified by the use of hydrogel spacers (use of spacer vs. no spacer used). Within each stratum, participants will be assigned in 1:1 ratio within each randomization block to one of the treatment arms:
Arm 1 (*n* = 150): The patient will undergo CT-guided SBRT.Arm 2 (*n* = 150): The patient will undergo MRI-guided SBRT.

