### Statistical analysis

#### Sample size

The PACE-B trial [4] and a multi-center SBRT trial run in the United States [14] provided the best estimate of acute grade ≥ 2 toxicities following modern SBRT. Extrapolating from these two trials, one would expect modern SBRT to have acute grade ≥ 2 GU and GI toxicity rates of 29.1 and 16.0%, and 5-year incidences of late grade ≥ 2 GU and GI toxicity of 13.3 and 2.0%. Based on a recently reported phase II study, MRI-guided SBRT may lead to acute grade ≥ 2 GU and GI toxicity rates of 19.8 and 3.0% [25]. Given that these results were based on an early MRI-guided SBRT experience and the PTV margin used in the MRI-guided arm in the current study is smaller (2 mm instead of 3 mm), it is reasonable to anticipate an acute grade ≥ 2 GU toxicity rate of closer to 15%.

The primary endpoint for this study is the incidence of acute grade ≥ 2 GU toxicity. The current study has been designed to detect a 14% reduction in acute toxicity, from 29 to 15%. An overall sample size of 300 patients (150 per arm) will provide 83.7% power to detect an absolute risk reduction of 14% with a one-sided, two-sample Z-test at a 0.025 significance level. Assuming an accrual of 75–100 patients per year, patients will be accrued over a period of 3.5 years and follow-up will continue for 5 years after the last subject is enrolled. However, the primary endpoint would be available for analysis 90 days after the final patient enrolled completes treatment. A trial designed to detect a smaller absolute difference in toxicity would be prohibitively large as for the expected difference, a trial of 300 patients is already required. Also given the cost of acquiring and operating an MRI-guided LINAC, one could also argue that a smaller absolute difference in toxicity would question the clinical relevance of the modality.

The study will also evaluate differences in the rate of acute grade ≥ 2 GI toxicity as well as the 5-year cumulative incidences of late grade ≥ 2 GU and GI toxicity. Other secondary endpoints include 5-year BCRFS (which will be stratified by risk group) and the proportion of fractions delivered that required online adaptation. Given the assumed toxicity rates, the absolute differences in the secondary toxicity endpoints that could be identified with 80% power, one-sided alpha 2.5% with *n* = 150 patients per arm are provided in Table 3.

**Table 3 Tab3:** Secondary endpoints power analysis

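### The primary test ignores the two factors that stratify randomisation and leaves Fisher's test open; naming one stratified test is a low-cost gain in efficiency

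*Protocol article*

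**What the plan says.** Under selection, enrolment and randomisation, the protocol article states that "stratified permuted blocked randomization will be used" and names the factors: "Randomization will be stratified by the baseline IPSS (≤15 or > 15) and prostate gland volume (≤50 cc or > 50 cc"). Allocation is balanced inside each stratum: "participants will be assigned in 1:1 ratio within each randomization block".

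Under analysis of the primary endpoint, the test is given as "Comparison between study arms will be performed via Chi-square test", or alternatively Fisher's exact test. No stratum or covariate is named, and no rule is given for choosing between the two tests.

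The sample size section uses a "one-sided, two-sample Z-test at a 0.025 significance level" and reports that 150 patients per arm "will provide 83.7% power to detect an absolute risk reduction of 14" percentage points, from 29% to 15%. That calculation is also unstratified, so the sizing and the chi-square option agree with each other.

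Stratified analysis is mentioned only for secondary endpoints: by hydrogel spacer for toxicity and bowel outcomes, and by risk group for biochemical recurrence-free survival.

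**The concern.** Balancing the arms within strata that predict the outcome reduces the true variance of the difference in proportions. The ordinary 2x2 test does not see this. It uses the marginal variance, which includes the between-stratum part that the randomisation has removed. Its p-values are then somewhat too large, and some of the precision gained by stratifying is not used.

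The unresolved choice between chi-square and Fisher is a second, separate loss. Fisher's test is conservative at this sample size even without strata, and it is not the test behind the stated power.

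What is at stake is efficiency. The sample size section itself says that a trial able to detect a smaller difference would be prohibitively large, so power that can be had without more patients is worth taking.

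**Working it through.** **Inputs from the protocol article.** Rates of 29% (CT) and 15% (MRI), 150 per arm, one-sided alpha 0.025, four strata, 1:1 within strata.

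**Inputs that must be assumed.** The share of patients in each stratum and the odds ratios of the two factors for acute GU toxicity. The documents give neither, so a range is shown.

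**Step 1: reproduce the plan's power.** Pooled two-sample Z-test with mean rate 0.22:

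- SE under the null = √(2 × 0.22 × 0.78 / 150) = 0.04783
- SE under the alternative = √((0.29 × 0.71 + 0.15 × 0.85) / 150) = 0.04715
- Power = Φ((0.14 − 1.960 × 0.04783) / 0.04715) = Φ(0.981) = 83.7%

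The stated figure reproduces.

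**Step 2: exact power of the two named tests, ignoring strata.** Enumerating both binomials at 29% and 15% with 150 per arm gives 84.1% for Pearson chi-square and 80.6% for two-sided Fisher, a gap of about 3.5 points. With a common rate of 22% or 29%, Fisher's actual two-sided size is 3.6% or 3.8% against a nominal 5%. Chi-square is at 5.0% in both cases.

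**Step 3: effect of ignoring the strata.** There were 200,000 simulated trials of 300 patients per scenario, with near-perfect 1:1 balance in each stratum. Both factors act on the log-odds scale, and overall rates are held at 29% and 15% (29% in both arms under the null). Tests are two-sided at 0.05. The Monte Carlo standard error is about 0.05 points for size and 0.08 points for power.

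| Odds ratio IPSS / volume | Assumed share IPSS >15 / volume >50 cc | Size: chi-square | Size: CMH | Power: chi-square | Power: CMH | Gain (points) |
|---|---|---|---|---|---|---|
| 1 / 1 | 20% / 35% | 5.0% | 5.0% | 84.2% | 84.1% | −0.1 |
| 1.5 / 1.3 | 20% / 35% | 4.9% | 5.0% | 84.2% | 84.3% | 0.1 |
| 2 / 1.5 | 20% / 35% | 4.7% | 4.9% | 84.3% | 84.8% | 0.5 |
| 2 / 2 | 30% / 40% | 4.5% | 5.0% | 84.6% | 85.3% | 0.8 |
| 3 / 2 | 20% / 35% | 4.2% | 4.9% | 84.8% | 86.1% | 1.3 |
| 4 / 3 | 30% / 40% | 3.6% | 5.0% | 85.7% | 88.3% | 2.6 |
| 5 / 3 | 50% / 50% | 3.4% | 5.0% | 85.8% | 88.7% | 2.9 |

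(Gains are taken from unrounded values.)

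**Step 4: check one row by hand.** For odds ratios 3 / 2 the stratum rates under the null are 0.196, 0.328, 0.422 and 0.594, with weights 0.52, 0.28, 0.13 and 0.07. The average within-stratum variance is Σ w p(1 − p) = 0.1923. The marginal variance is 0.29 × 0.71 = 0.2059. The ratio is 0.934, so the chi-square test behaves as if its critical value were 1.960 / √0.934 = 2.028, which has a two-sided size of 4.3%. The simulation gave 4.2%.

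**The case against.** The strongest reply is that nothing promised is lost. The trial was sized with an unstratified test, and the unstratified chi-square keeps at least 84% power in every scenario, above the stated 83.7%. That stands. The stratified test adds an optional gain and repairs no shortfall.

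A reader might infer that the primary test is invalid because its error rate is not nominal. The departure is only downward, so there is no added risk of a false positive.

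A reader might also take the two factors as having been chosen because they drive GU toxicity, and so expect the larger gains. The article gives no reason for choosing them and no association with acute GU toxicity. If they are weak predictors, the two tests are practically the same.

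Nor can one say that the planned confidence interval for the treatment difference is too wide. The article promises point estimates with 95% intervals for toxicity rates, which may mean each arm separately, and fixes no interval for the difference.

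On Fisher, the wording can be read as the usual shorthand for using it when expected counts are small. With 150 × 0.22 = 33 events expected per arm it would not normally be triggered, and a fuller document may hold the rule. Even so, 80.6% exceeds 80%. This softens the point, but the article as written permits Fisher without a condition.

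Finally, the article says that secondary toxicity analyses are further stratified by spacer, and its repeated-measures model allows other baseline covariates. Those analyses may already carry the randomisation factors, so the point is confined to the primary endpoint.

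**Conclusion.** The point holds as an efficiency improvement, not as a validity error. The article stratifies randomisation by IPSS and gland volume and then fixes a primary comparison that uses neither.

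The direction is certain if the strata are prognostic: the unstratified test is mildly conservative. The size depends on assumed stratum effects and prevalences. The power forgone is under 1 point for odds ratios up to 2 for each factor, and about 3 points for very strong ones.

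The Fisher option needs no assumption about strata. It costs about 3.5 points against chi-square and puts power about 3 points below the stated 83.7%. Under most of the assumed scenarios that is more than the loss from ignoring the strata.

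**What to change.** Name one primary test: a Cochran-Mantel-Haenszel test over the four IPSS-by-volume strata at one-sided 0.025, which matches the sample size section and is equivalent to two-sided 0.05. Report the Mantel-Haenszel stratified risk difference with its 95% CI as the primary estimate. Keep the unstratified chi-square as a sensitivity analysis, and drop Fisher's test for the primary endpoint.

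The cost is analysis wording only. Both factors are known at randomisation, and no patients or data are added. If the strata prove not to be prognostic, the stratified test gives up essentially nothing (84.1% against 84.2%). The sample size statement can stay as it is.

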#### Analysis of secondary endpoints

Secondary endpoints include the incidence of acute grade ≥ 2 GI toxicity on the CTCAE v 4.03 scale. Other secondary endpoints include 5-year cumulative incidences of late grade ≥ 2 GU and GI toxicity based on the CTCAE v 4.03 scale, which will be analyzed using a cumulative incidence framework. The analysis of both acute and late GI toxicity will be stratified for the use of hydrogel spacers or not, as these may reduce both acute and late GI toxicity.

Patient-reported outcomes on various QOL instruments will be other secondary endpoints of interest. Utilizing the EPIC-26 instrument, one can assess changes from baseline in domains such as urinary incontinence/ obstruction, bowel symptoms, sexual function, and hormone/vitality domains. Based on the magnitude of the changes, a determination can be made whether they represent minimally important differences [26]. As to the IPSS and SHIM QOL indices, both the numerical change from baseline, as well as the raw score at any given timepoint, will be collected and reported descriptively. A restricted maximum likelihood (REML)-based mixed models repeated measures (MMRM) approach will be used for analysis of QOL. The model will include time, fixed categorical effects of treatment, treatment-by-time interaction, and other fixed baseline covariates. In order to model the within-patient errors, an unstructured covariance structure will be employed. Kenward-Roger approximation will be used to estimate denominator degrees of freedom. The analysis of both acute and late changes in the bowel domain of the EPIC instrument will be stratified for the use of hydrogel spacers or not, as these may reduce both acute and late GI bowel symptoms. The impact of pelvic nodal irradiation on toxicities will be included as a pre-specified, albeit post-hoc analysis, as the decision is per investigator’s discretion pending achievable dosimetry, which may not be known until after randomization and simulation.

Kaplan-Meier statistics as well as descriptor statistics (such as mean, median, standard deviation, quartile range) will be ysed to estimate 5-year BCRFS. Figures showing the Kaplan-Meier estimates will also be presented. Death of any cause will be treated as a competing risk. Comparison of five-year BCRFS between study arms will be performed by log-rank test.

Point estimate and the corresponding 95% CIs will be calculated to determine the proportion of SBRT fractions for which online adaptive radiotherapy is required due to changes in OAR anatomy.

Imputation will not be used to handle missing data.

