#### Secondary endpoints

The incidence of acute grade ≥ 2 GI toxicity as assessed by the CTCAE version 4.03 scale. The timeframe will be restricted to the first 90 days after SBRT.The 5-year cumulative incidences of late grade ≥ 2 GU and GI physician-reported toxicity, as assessed by the CTCAE version 4.03 scale.The temporal changes in patient-reported QOL outcomes will be obtained depending on the instrument used. For the Expanded Prostate Cancer Index-26 (EPIC-26) instrument, these will be represented by changes from baseline in the urinary incontinence, urinary obstruction, bowel, sexual function, and hormone/vitality domains. Changes will be analyzed with respect to whether they represent minimally important differences [26]. For the IPSS and Sexual Health Inventory for Men (SHIM) instruments, the numerical change from baseline, as well as the raw score at any given timepoint, will be extracted.Five-year BCRFS, with biochemical recurrence (BCR) defined as serum PSA levels that are 2 ng/mL higher than the nadir PSA achieved after SBRT.The proportion of fractions of MRI-guided SBRT in which online adaptive radiotherapy was used.

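### The Kaplan-Meier estimate of 5-year biochemical recurrence-free survival does not match the stated handling of death, and mean and SD cannot estimate it

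*Protocol article*

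**What the plan says.** Under Secondary endpoints the outcome is given as "Five-year BCRFS, with biochemical recurrence (BCR) defined as serum PSA levels that are 2 ng/mL higher than the nadir PSA achieved after SBRT". That fixes the PSA event and is silent on death.

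Under Analysis of secondary endpoints, four consecutive sentences set out the analysis:

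- Estimation: "Kaplan-Meier statistics as well as descriptor statistics (such as mean, median, standard deviation, quartile range) will be ysed to estimate 5-year BCRFS".
- Display: "Figures showing the Kaplan-Meier estimates will also be presented".
- Death: "Death of any cause will be treated as a competing risk".
- Comparison: "Comparison of five-year BCRFS between study arms will be performed by log-rank test".

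The Sample size section adds a further feature, "5-year BCRFS (which will be stratified by risk group", which the log-rank sentence does not repeat. The analysis section assigns late toxicity to a cumulative incidence method but does not do so for BCRFS.

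**The concern.** Kaplan-Meier handles one kind of event. If death counts as that event, the curve is a recurrence-free survival curve and death does not compete with anything. If death is a competing risk, the observable probability of recurrence by 5 years is the cumulative incidence function. A Kaplan-Meier curve that censors deaths instead describes a hypothetical population in which nobody dies first. The paragraph names the estimator and the handling of death without joining them, and the endpoint definition does not settle which is meant.

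Mean and SD are a separate fault. With censored follow-up they do not estimate the proportion event-free at 5 years.

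What is at stake is the meaning of the reported 5-year percentage. BCRFS is the only oncologic outcome among the secondary endpoints, and the arms typically use different margins (2 mm MRI, 4 mm CT, under Radiotherapy contouring and planning), so readers will look at it. The trial is open-label and the data analysts know the assignment, so the choice is better made before outcomes are seen.

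**Working it through.** **Plan's own figure.** The protocol states no assumed rate, event count or power for BCRFS, so there is none to reproduce. The primary power does not depend on BCRFS. With 150 per arm, 29% against 15% and one-sided 0.025, the pooled Z-test gives 83.67%, against 83.7% stated.

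**Inputs (assumptions, not from the documents).** Constant, independent hazards over 5 years; net 5-year recurrence b = 10%; net 5-year death d = 5% or 10%. Write B = -ln(1 - b) and D = -ln(1 - d) for the 5-year cumulative hazards.

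**Three quantities that could be reported as 5-year BCRFS**

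- Kaplan-Meier, deaths censored: exp(-B) = 1 - b.
- One minus cumulative incidence, death competing: 1 - [B/(B + D)] × [1 - exp(-(B + D))].
- Composite, death an event: exp(-(B + D)) = (1 - b)(1 - d).

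**Death 5%.** B = 0.1054, D = 0.0513.

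- Kaplan-Meier: 90.0%.
- Cumulative incidence: (0.1054/0.1567) × 0.145 = 9.75%, so one minus it is 90.25%.
- Composite: 0.90 × 0.95 = 85.5%.

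**Death 10%.** B = D = 0.1054.

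- Kaplan-Meier: 90.0%.
- Cumulative incidence: 0.5 × 0.19 = 9.5%, so one minus it is 90.5%.
- Composite: 0.90 × 0.90 = 81.0%.

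**Gaps**

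| Comparison | Death 5% | Death 10% |
|---|---|---|
| Recurrence risk overstated by Kaplan-Meier with deaths censored | 10.0 - 9.75 = 0.25 points | 10.0 - 9.5 = 0.5 points |
| Composite below Kaplan-Meier with deaths censored | 90.0 - 85.5 = 4.5 points | 90.0 - 81.0 = 9.0 points |
| Composite below one minus cumulative incidence | 90.25 - 85.5 = 4.75 points | 90.5 - 81.0 = 9.5 points |

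Over wider assumed ranges (net recurrence 5-15%, death 3-10%), the first gap runs from about 0.1 to 0.7 points and the third from 2.8 to 9.8 points.

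**Arm difference.** Assume net recurrence of 10% in one arm and 15% in the other, with 10% death in both. The second arm has one minus cumulative incidence 85.74% and composite 0.85 × 0.90 = 76.5%.

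- Kaplan-Meier, deaths censored: 90.0 - 85.0 = 5.0 points.
- Cumulative incidence: 90.5 - 85.74 = about 4.8 points.
- Composite: 81.0 - 76.5 = 4.5 points.

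So the choice mainly moves the level. It moves the contrast little, provided death is equally frequent in both arms.

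**The case against.** The strongest reply is that the text already says how death is handled. Since it names death as a competing risk and the definition names only the PSA event, the composite is suggested by nothing but the word *survival* in the label. On that reading only the 0.25-0.5 point gap remains. This largely stands, and the larger gap should not be presented as the error in the plan. It is what separates the two meanings if the label is taken literally.

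Three stronger inferences are tempting, and the documents do not support them:

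- A reader might infer that the log-rank test is invalid here. With deaths censored it validly tests the cause-specific hazard of recurrence, so it is compatible with competing risks.
- A reader might infer that the test is declared unstratified, in contradiction of the Sample size section. The analysis section is silent on stratification, and stratifying by risk group could mean either a stratified test or reporting by group.
- A reader might infer that every listed descriptor is unusable. The median and quartiles can be read from a Kaplan-Meier curve that falls far enough; only mean and SD clearly fail.

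It is also fair to say that BCRFS is secondary and carries no hypothesis or power. Under Early stopping guidelines it is looked at in the interim analysis, but the halting and termination thresholds attach only to grade 3 or higher GU and GI events. The protocol does not call BCRFS a check on the smaller MRI margin; that use is an inference. None of this reconciles Kaplan-Meier estimation with death as a competing risk, and because both are stated, the mismatch is not a detail left to an analysis plan.

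**Conclusion.** The point holds as a mismatch between the stated estimator and the stated handling of death, together with two unsuitable summary statistics. A reader might go further and infer that 5-year BCRFS has no valid estimate at all. It does: each quantity is estimable once chosen, and the text simply fails to fix which one is meant.

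The size depends on that choice. The effect is a fraction of a point if death competes, and 4.5-9 points in the reported level if a composite was intended. Both figures rest on assumed rates of 10% net recurrence and 5-10% death with constant, independent hazards. The small effect on the arm difference further assumes equal death rates. This is a secondary-endpoint correction of modest weight; the primary endpoint, its test and its power are untouched.

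**What to change.** Choose one definition before outcome data are seen and match the method to it.

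1. **Recurrence as the event, death competing.** Estimate by the cumulative incidence function with a 95% CI at 5 years, and compare arms by Gray's test or a cause-specific log-rank test. The label should then say cumulative incidence of biochemical recurrence. This is closest to the present sentence on death.
2. **Recurrence or death as the event.** Keep Kaplan-Meier and log-rank, delete the competing-risk sentence, and report the cumulative incidence of recurrence alongside.

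Both are valid. In either case, drop mean and SD as estimators of 5-year BCRFS, and carry the risk-group stratification from the Sample size section into the comparison. Apply the same definition to the interim look at BCRFS.

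The cost is a few sentences and, under the second option, one extra standard analysis. It needs no change to sample size or visit schedule.
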